### Economic evaluation

Only health care (acute) resources are considered. Intervention costs are obtained with a bottom-up microcosting approach that identifies all relevant cost components of the telephone intervention and values each of those components for all individual patients using the following variables: duration, staff, and equipment. Consultations, sick leave, drugs and other resources and emergency interventions for each patient are recorded in the electronic Case Report Form (eCRF) or retrieved from the hospital databases. The prices of drugs, consultations and an emergency ambulance are based on national tariffs. Hospitalisation costs are estimated from the average national cost of each patient’s diagnosis-related groups weighted with their actual length of stay and resources used during their hospitalisation (intensive care, blood transfusion, etc.). The time horizon is 15 days.

For the purpose of the cost-effectiveness analysis, we define a composite endpoint of adverse events combining hospital admissions, emergency visits and 15-day mortality. A cost-effectiveness analysis is conducted to assess incremental cost per adverse event averted. The cost-effectiveness analysis focusses on estimation of the joint density of cost and effect differences and quantification of uncertainty surrounding the incremental cost-effectiveness ratio. The absence of a significant difference in either cost or effectiveness, or both, does not preclude the presentation of such data on the cost-effectiveness plane [15, 16].

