### Outcomes

The primary endpoint is the percentage of patients receiving an out-of-hours, face-to-face consultation with a GP, or who are admitted to hospital, during the 2 weeks following their call to the centre. The motive for the consultation or hospital admission should be the same as the motive initially prompting the call. Secondary endpoints are the following variables measured over the 2 weeks: number of stays in intensive care, number of hospital admissions, number of interventions by the fire brigade, emergency medical and ambulance services, number and length of prescribed sick leave episodes, all-cause mortality, morbidity, clinical outcome, patient compliance, patient satisfaction, number of renewed calls to the call centre, number of patients receiving multiple face-to-face consultations and costs incurred.

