### Statistical analyses

Analyses will be intent-to-treat (ITT). Any missing values for the primary endpoint will be computed by the multiple imputation method. In which case, the robustness of the conclusions made on observed cases will be verified and a possible discrepancy will be analysed based on any biases in data collection that may have been identified.

Descriptive analyses will provide the following information for each continuous variable: mean value, standard deviation, 95 % confidence intervals (95 % CI), minimum, 1st quartile, median, 3rd quartile and maximum, and number of missing observations. Categorical variables will be summarised in frequency tables (with 95 % CI). Intracluster correlation coefficients will be calculated.

The primary endpoint will be tested using the Generalised Estimating Equations model, account being taken of the cluster trial design. Secondary continuous endpoints will be analysed with a mixed-model ANOVA including a random centre effect. For categorical variables, treatment effect will be tested using the Generalised Estimating Equations model, account being taken of the cluster trial design. All tests will be two-tailed with a 5 % alpha risk. All statistical tests will be performed using SAS version 9.2 software.

The health economic analysis will consider total cost, hospital costs, ambulatory costs, cost borne by the family and costs to society. Analysis of management costs in both study arms will be ITT. Cost comparisons will be performed using appropriate statistical methods after determining the type of distribution (normal, log normal or beta).

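### The article gives two incompatible cost perspectives and two unreconciled rules for comparing costs, so the numerator of the cost-effectiveness ratio is not fixed

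*Protocol article*

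**What the plan says.** **Perspective.** The Economic evaluation section opens with "Only health care (acute) resources are considered". The same paragraph lists what is collected: "Consultations, sick leave, drugs and other resources and emergency interventions for each patient are recorded in the electronic Case Report Form (eCRF". It values the telephone intervention by microcosting and hospital stays by national average costs. For other items, "The prices of drugs, consultations and an emergency ambulance are based on national tariffs". The Statistical analyses section then says "The health economic analysis will consider total cost, hospital costs, ambulatory costs, cost borne by the family and costs to society".

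**Target.** The Economic evaluation section seeks the extra cost for each adverse event avoided, and adds that "The cost-effectiveness analysis focusses on estimation of the joint density of cost and effect differences".

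**Method for costs.** The Outcomes section ends its list of secondary endpoints with "number of patients receiving multiple face-to-face consultations and costs incurred". Two sentences under Statistical analyses can therefore apply to costs. The general one is "Secondary continuous endpoints will be analysed with a mixed-model ANOVA including a random centre effect". The cost-specific one is "Cost comparisons will be performed using appropriate statistical methods after determining the type of distribution (normal, log normal or beta".

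**The concern.** A ratio of extra cost to events avoided has one numerator, and the perspective defines it. Here one section restricts that numerator to acute health care, while another extends it to families and society. The intervention aims to replace out-of-hours visits with home management and a later office-hours appointment. Family costs and sick leave could therefore move differently from acute-care costs. With both perspectives in the text and neither named as base case, a reader of the final report could not tell which one was intended before the results were known.

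The second problem concerns the method. The cost-specific sentence lets the observed distribution decide the comparison. It does not say that the quantity compared is the arithmetic mean cost, nor how the six centres enter the analysis. It also does not say whether it replaces the general rule for continuous secondary endpoints or adds to it.

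**Working it through.** **1. Perspectives side by side.**

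| Cost item | Economic evaluation section | Statistical analyses section |
|---|---|---|
| Hospital and ambulatory care | included, valuation stated | included |
| Sick leave | recorded, but not an acute health-care resource | would fit under societal cost |
| Family costs | excluded by the word *only* | included |
| Costs to society | excluded by the word *only* | included |

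No other section reconciles the two columns. The valuation methods in the article cover the intervention, drugs, consultations, ambulance and hospital stays, which fits the narrower perspective. The recording of sick leave fits the wider one.

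**2. Rules for costs side by side.** The general rule is fixed in advance, compares means and has a random centre effect. The cost-specific rule is chosen after looking at the distribution and names no test, estimand or cluster adjustment. Of its three candidates, the standard beta distribution lies between 0 and 1, so it is an odd choice for amounts in currency unless costs are rescaled.

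**3. What the log-normal branch would do if run as a test on log costs.** Such a test compares geometric means. For a log-normal cost with log-scale mean μ and standard deviation σ, the arithmetic mean is exp(μ + σ²/2). If the geometric means are equal, the ratio of arithmetic means is exp((σ₂² − σ₁²)/2). The documents give no log-SDs, so these are assumed, with σ₁ = 1.0:

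- σ₂ = 1.1: exp((1.21 − 1.00)/2) = 1.11
- σ₂ = 1.2: exp((1.44 − 1.00)/2) = 1.25
- σ₂ = 1.3: exp((1.69 − 1.00)/2) = 1.41

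Conversely, with σ₂ = 1.3 and equal arithmetic means, the geometric mean ratio is exp(−0.345) = 0.71. With equal log-SDs the discrepancy vanishes.

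**4. The design effect and what it is for.** The article gives no sample size or variance for costs. Its design effect of 1.5 belongs to the primary endpoint, as its own calculation shows. For 50% versus 40%, two-sided 5% and 85% power, the pooled formula gives (1.96·√(2·0.45·0.55) + 1.036·√(0.25 + 0.24))²/0.10² ≈ 443 per arm. Multiplying by 1.5 gives 664.5, against 663 stated.

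**5. Illustration: clustering ignored for costs.** Inputs are design effect DE and a normal reference distribution.

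- Understatement of the standard error: 1 − 1/√1.5 = 1 − 0.816 = 18%.
- Type I error of a nominal 5% test: 2·(1 − Φ(1.96/√1.5)) = 2·(1 − Φ(1.600)) = 11.0%.

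The ICC of costs is not given. With about 240 patients per centre and indication, DE = 1 + 239·ICC. Assumed values give:

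| Assumed ICC | DE | Type I error |
|---|---|---|
| 0.005 | 2.195 | 18.6% |
| 0.01 | 3.39 | 28.7% |
| 0.02 | 5.78 | 41.5% |
| 0.05 | 12.95 | 58.6% |

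These figures do not include the further small-sample problem of three centres per arm.

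**The case against.** The two perspective statements might serve different purposes: acute health care for the cost-effectiveness ratio, and the wider list for descriptive cost comparisons. That would be a sensible plan, but the article does not say so, and sick leave sits inside the narrower section. The contradiction stands.

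The objection is stronger on the method. A reader might infer that the plan drops clustering for costs. The documents do not support that: costs are a secondary endpoint, and continuous secondary endpoints get a model with a random centre effect. The cost-specific sentence is silent on clustering and does not remove it. A reader might also infer that the plan does not target mean cost. That too goes beyond the text. The general rule compares means, the economic section aims at incremental cost, no log-scale test is named, and a log-normal model can be used to estimate an arithmetic mean.

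A condensed article may also leave the exact cost model to a full protocol or a health economic plan. The absence of that detail is therefore not the finding. What remains is what is printed: two rules that could each govern costs, one of them explicitly dependent on the observed distribution, with no statement of which prevails.

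**Conclusion.** The point holds in two parts. The firm part is the contradiction on perspective, which leaves the numerator of the ratio undefined and open to choice after the results. Its size cannot be computed, because the documents contain no cost figures. A claim that it could reverse the sign of the incremental cost would be conjecture.

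The second part is narrower: costs have two unreconciled analysis rules, and the cost-specific one is data-driven and leaves the estimand and cluster handling open. Its log-normal branch would miss the required arithmetic means only if carried out as a test on log costs. The mean ratios of 1.11 to 1.41 rest on assumed log-SDs. The 18% understatement and 11% type I error apply only if clustering were ignored, and they borrow a design effect set for a binary endpoint. They show why the rule should be fixed and are not a forecast of error in this trial. The point should be acted on, but it concerns a secondary endpoint and leaves the primary analysis untouched.

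**What to change.** - **Perspective.** State one base case for the ratio, for example the acute health-care perspective of the Economic evaluation section. Report family and societal costs, including sick leave, as a separate and labelled secondary analysis.
- **Method.** Replace the distribution-driven choice with a pre-specified between-arm difference in arithmetic mean cost. Account for centre clustering with a small-sample correction for six centres, for instance centre-level means on 6 − 2 = 4 degrees of freedom, or a linear or gamma model with a corrected cluster variance. State that this rule governs costs in place of the general one.
- **Joint uncertainty.** Carry the same clustering into the joint distribution of cost and effect differences.

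The Discussion says that the economic evaluation had yet to start, so this can be a dated change of wording made before cost results by arm are seen. It needs modest coding and no new patients. The price is wider intervals: at 4 degrees of freedom the two-sided 5% critical value is 2.776 instead of 1.960, a factor of 2.776/1.960 = 1.42 for the same standard error.

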### Data collection

Inclusion becomes effective when the person telephoning the call centre agrees to data collection and to a follow-up call.

The Case Report Form (CRF) is completed by the investigator at the call centre. It gives the caller’s and/or patient’s identification details (initials, date of birth, sex, relationship to the patient and the centre’s allocated patient number), inclusion and exclusion criteria, the medical indication for the call (fever or symptoms of gastroenteritis), and the caller’s reason for calling (request for advice, for a physician, etc.). The CRF also contains data on the following: how the call is handled by the centre (time taken, number of calls on hold whilst handling the call, the patient’s history, handling according to study arm), self-evaluation of performance by the call centre’s physician, foreseeable delay before any intervention by an on-duty GP at the caller’s home, and the names and postal codes of localities with the closest emergency facilities, duty GP and duty pharmacist.

A follow-up telephone call will be made 15 ± 4 days after the index telephone call (D0), regardless of study arm, by a clinical trial technician (CTT) trained by the trial investigator at the coordinating centre. The CTT will record the following: date, time and duration of follow-up call, the patient’s environment (rural or urban), answers to a satisfaction questionnaire on call handling on D0, a clinical evaluation of the patient (compliance, course), and all data required for the health economic evaluation. If the patient is underage and/or unable to answer the questions, only the caller will be interviewed. The patient will be considered lost-to-follow-up if there is no reply after a series of 15 calls.

All data will be archived as an eCRF under the responsibility of the Clinical Research Unit of Lariboisière-Saint Louis, Paris, France. The paper versions of the CRF will be kept in safe keeping in each centre for a period of 15 years.

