**Methods/design:**

This is a prospective, open-label, multicentre, pragmatic, cluster randomised clinical trial of an estimated 2880 patients making an out-of-hours call to one of six French emergency call centres for assistance with either fever or symptoms of gastroenteritis without seriousness criteria. Each call is handled by a call centre physician. Out-of-hours is 8 p.m. to 7.59 a.m. on weekdays, 1 p.m. to 7.59 a.m. on Saturdays and round-the-clock on Sundays and school holidays. Patients will be enrolled over 1 year.

In the intervention arm, a telephone consultation based on a protocol, the formal Telephone Medical Advice (fTMA), is offered to each patient calling. This protocol aims to overcome a physical consultation during out-of-hours periods. It offers reassurance and explanations, advice on therapeutic management which may include, in addition to hygiene and diet measures, a telephone prescription of antipyretic, analgesic, rehydration medication or others, and recommendations on surveillance of the patient and any action to be taken. The patient is invited to call again if the condition worsens or new symptoms develop and to make an appointment with their family GP during office hours. In the control arm, the call centre physician handles calls as usual. This physician can carry out a telephone consultation with or without a telephone prescription, dispatch an on-duty GP, the fire brigade or an ambulance to the patient, or refer the patient to an on-duty physician or to the ED. Each patient will receive a follow-up call on day 15.

The primary endpoint is the frequency of out-of-hours, face-to-face GP consultations or visits to the ED during the 15 days following the index call. The secondary endpoints measured on day 15 are the number of stays in intensive care, the number of hospital admissions, the number of interventions by the fire brigade, emergency medical and ambulance services, the number and length of prescribed sick-leave episodes, all-cause mortality, morbidity, clinical outcome, patient compliance, patient satisfaction, the number of renewed calls to the call centre, the number of patients receiving multiple face-to-face GP consultations and costs incurred.

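### The follow-up call may be made from day 11, before the 14- or 15-day endpoint window has closed, so compliant early calls cannot observe the whole endpoint

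*Protocol article*

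**What the plan says.** The Data collection section describes one follow-up contact: "A follow-up telephone call will be made 15 ± 4 days after the index telephone call (D0". It is made "regardless of study arm, by a clinical trial technician (CTT" in the document's abbreviation, a technician trained by the trial investigator at the coordinating centre. The items listed for that call begin: "The CTT will record the following: date, time and duration of follow-up call".

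The period to be observed is given in two lengths. The Outcomes section defines the primary endpoint "during the 2 weeks following their call to the centre" and adds "Secondary endpoints are the following variables measured over the 2 weeks". The abstract gives the primary endpoint as "during the 15 days following the index call". The Economic evaluation section says "The time horizon is 15 days".

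For the economic resource data, the same section says that items "are recorded in the electronic Case Report Form (eCRF) or retrieved from the hospital databases". No second source is named for the primary endpoint. The Statistical analyses section plans multiple imputation for missing primary-endpoint values and does not mention windows that are only partly observed.

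**The concern.** The tolerance around the call is symmetric, but the endpoint is a count over a fixed period that ends at about the nominal call date. A tolerance on the early side therefore cuts into the period being measured. A patient reached on day 11 can report only what has happened by day 11.

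For the binary primary endpoint the difficulty is confined to early calls that report no event. An early call that already reports a qualifying event is complete. An early call with no event looks like an observed absence, so nothing in the text marks it as missing or sends it to the planned imputation. For costs and for the endpoints that count events, any early call can be incomplete.

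The stake is an event rate somewhat below the one defined, with a correspondingly smaller absolute difference between arms. No analysis rule can recover days that had not yet occurred when the call was made, so the early limit is best settled in the protocol.

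**Working it through.** **Inputs from the document.** Call at 15 ± 4 days (Data collection). Window of 14 days (Outcomes) or 15 days (abstract, Economic evaluation). Planned rates 50% and 40%; 663 patients per arm per indication; design effect 1.5; 85% power; 5% alpha (Sample size); two-tailed tests (Statistical analyses).

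**Step 1: call days.** 15 − 4 = 11 and 15 + 4 = 19.

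**Step 2: days left unobserved (window length minus call day).**

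| Call day | 14-day window | 15-day window |
|---|---|---|
| 11 | 3 (3/14 = 21%) | 4 (4/15 = 27%) |
| 12 | 2 (14%) | 3 (20%) |
| 13 | 1 (7%) | 2 (13%) |
| 14 | 0 | 1 (7%) |
| 15-19 | 0 | 0 |

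This step rests only on the document's figures.

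**Step 3: effect on the rates under an assumed late share.** The document does not say when events occur. Let s be the share of first events after day 11, equal in both arms, and let every call be on day 11. The observed rate is the true rate × (1 − s).
- s = 2%: 50 × 0.98 = 49.0 and 40 × 0.98 = 39.2; difference 9.8 points.
- s = 10%: 50 × 0.90 = 45.0 and 40 × 0.90 = 36.0; difference 9.0 points.

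The control rate falls by 1 to 5 points, but the contrast falls by only 0.2 to 1.0 point, towards no difference. Both are upper ends for a given s, because not every call will be on day 11.

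**Step 4: power, as a scale.** The plan's figure first: the usual pooled two-proportion formula for 50% versus 40%, two-sided 5%, 85% power gives 443 per arm, and 443 × 1.5 = 664.5, close to 663. (That match leaves out the 15% loss to follow-up; this is a separate matter and does not affect this point.) The effective size is 663/1.5 = 442 per arm, with power 85%.

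The captured share for a day-11 call and window W is 11/W if events are spread evenly, or (1 − e^(−11/m))/(1 − e^(−W/m)) if event times are exponential with mean m days. Both timings are assumptions. If all calls were on day 11:

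| Event timing | Captured (W = 14 / 15) | Contrast, points | Power |
|---|---|---|---|
| Even spread | 79% / 73% | 7.9 / 7.3 | 69% / 64% |
| Mean 5 days | 95% / 94% | 9.5 / 9.4 | 81% / 81% |
| Mean 3 days | 98% / 98% | 9.8 / 9.8 | 84% / 84% |
| Mean 2 days | 99.7% / 99.7% | 10.0 / 10.0 | 85% / 85% |

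If calls were instead spread evenly over days 11-19 and events cut off at the window, the captured share would be 95% / 93% under even spread and 99% / 98% with a mean of 5 days.

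Even spread is an extreme for this population. Symptoms must have begun within the previous 72 hours, and the consultation must have the same motive as the index call, so early events are more plausible.

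**The case against.** A tolerance of a few days around a follow-up call is ordinary in a pragmatic trial, and it helps to reach people who may need up to 15 attempts. In an acute illness most events probably come early, so little is lost. This stands as an argument about size. It does not remove the mismatch, because a tolerance on the late side only would serve the same purpose.

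Hospital databases may recover admissions and emergency visits. That stands in part: they are named for the economic resource data, and they would not show out-of-hours GP consultations, which are a main component of the primary endpoint.

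A reader might also infer stronger points that the document does not support:
- **Late calls inflate the endpoint.** The endpoint definitions and the cost horizon already exclude later events; the ± 4 days governs the interview, not the counting period. Whether events are dated and filtered is a detail that an article commonly leaves to the case report form or analysis plan.
- **Early patients are scored as event-free.** No scoring rule for a partly observed window is stated either way.
- **Three centres per arm turn call timing into an arm difference.** The call is specified identically for both arms and is not made by the call-centre physician. Nothing shows that timing differs by centre or arm.
- **Sick leave and costs are hit harder.** The endpoint is prescribed sick leave, whose length may be known before it has elapsed, and resource data have a second source. The document gives no basis for a larger effect.

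**Conclusion.** The point holds in a limited form. The early limit of the call window contradicts the length of the endpoint: a compliant call can leave up to 21% of a 14-day window or 27% of a 15-day window unobserved, and nothing in the document repairs this for out-of-hours GP consultations. That part needs no assumption.

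The consequence is probably small: a modest under-count of events and costs and slight dilution of the contrast. With 2-10% of events after day 11 and all calls on day 11, both assumed, the contrast shrinks from 10 points to between 9.8 and 9.0. The fall in power to 69% or 64% needs evenly spread events and every call on day 11 together, and should not be read as an expected loss. The 1-5 point loss is in the control-arm rate among day-11 calls; it is not an error in the treatment difference. Bias between arms remains conditional on a difference in call timing that the document does not show. This is a worthwhile inexpensive improvement and does not threaten the trial's conclusion.

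**What to change.** 1. State one endpoint length, 14 or 15 days, in the abstract, Outcomes, Sample size and Economic evaluation sections.
2. Make the follow-up call no earlier than the end of that window, for example 0/+4 days. Since 11-19 offers nine contact days and 15-19 offers five, a later upper limit (0/+8 would keep nine) preserves the opportunity to reach patients.
3. Count only events and costs dated within the window.
4. Inclusion had ended and follow-up was still running when the article appeared. For early calls already made with no event reported, re-contact the patient where possible. Otherwise treat the endpoint as incompletely observed in the planned multiple imputation, conditioning on no event up to the call day. Imputing the whole endpoint afresh would discard the event-free days already known and overstate the rate.
5. Add a sensitivity analysis restricted to events on days 0-11, which every compliant call covers.

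**Cost.** Items 1 to 3 are wording and a date filter. Items 4 and 5 need some technician time, a change to the imputation and one extra analysis. Recall is slightly longer for some callers, and a few more patients may go unreached if the upper limit is not extended.
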